### 3. STUDY POPULATION

Subjects should be clinically diagnosed as HIV Lipodystrophy with confirmed diagnosis of HIV 1 and on highly active antiretroviral therapy (HAART) for at last 18 months with Triglyceride level ranging between 200 to 500 mg% .before getting enrolled in the trial.

#### 3.1 NUMBER OF SUBJECTS PLANNED

The required sample size for this study to achieve 80% power at the 5% level of significance is a total of 50 subjects.

#### 3.2 CRITERIA(S) FOR INCLUSION AND EXCLUSION

##### Inclusion Criteria (s):

- Age 18- 65 years
- Subjects should have confirmed diagnosis of HIV 1 and on highly active antiretroviral therapy (HAART) for at last 18 months.
- On stable ART regimen for at least 8 weeks prior to inclusion in the study and ART regimen not expected to change in next 3 months.
- Subjects clinically diagnosed as HIV Lipodystrophy (at least 1 moderate or severe Lipodystrophy feature identified by doctor and patient, except isolated abdominal obesity)
- Triglycerides between 200 – 500 mg%
- Subject has given informed consent for participation in this trial
- Subjects whose CD4 count is  $> 50/\text{mm}^3$

##### Exclusion Criteria(s):

- Subjects on insulin and/or glitazone / glitazar therapy
- Pregnancy and lactation
- Subjects with history of gall stone.

|                                                         |                                                 |                                                           |
|---------------------------------------------------------|-------------------------------------------------|-----------------------------------------------------------|
| Prepared by:
[name]
Date: 22.06.2010 | Approved by:
[name]
Date:22.06.2010 | Protocol No. ZYH1.09.003.01 .PROT
Version No.: 1.0 (R) |
|---------------------------------------------------------|-------------------------------------------------|-----------------------------------------------------------|

|                                                                                  |                                                                                           |              |
|----------------------------------------------------------------------------------|-------------------------------------------------------------------------------------------|--------------|
| [figure not shown] | Clinical trial Protocol for ZYH1 – Phase II
ZYH1.09.003.01.PROT

DCGI Submission | Confidential |
|----------------------------------------------------------------------------------|-------------------------------------------------------------------------------------------|--------------|

- Subjects with history of Cardiac failure.
- Subject with history of alcohol and/or drug abuse
- History of allergy, sensitivity or intolerance to the study drugs and their formulation ingredients.
- Active Opportunistic infection in last three months.
- History of malignancy or active neoplasm.
- Any active hormonal disease and/or hormonal treatment that may affect the outcomes of interest such as clinically overt hypo/hyperthyroidism, hypogonadism, hypercortisolism, or treatment with steroids or growth hormone.
- Hemoglobin below 9 g/dl or Total leucocyte count below 1000/mm^3 or Platelet count below 50,000/mm^3
- Subjects with history of myopathies or evidence of active muscle diseases or CPK ≥10 times UNL
- Subjects with history of active liver disease or hepatic dysfunction demonstrated by aspartate aminotransferase (AST) and alanine aminotransferase (ALT) ≥2.5 times of upper limits of normal or Bilirubin more than 2 times UNL
- Renal dysfunction (serum creatinine > 2 mg%)
- Participation in any other clinical trial in past 3 months

### 3.4 WITHDRAWAL CRITERIA

The investigator may withdraw a subject from the study for any of the following:

- Subject who reports serious AEs (SAE)
- Subject who develops any serious/severe diseases which requires admission in intensive care unit (ICU) or interventional surgery, even if it is not related with investigational drugs
- Any subject found to have entered the study in violation of this protocol or if the subject is uncooperative during the study.
- Any subject who interrupts the study medication for longer than 4 consecutive days.

|                                                         |                                                 |                                                           |
|---------------------------------------------------------|-------------------------------------------------|-----------------------------------------------------------|
| Prepared by:
[name]
Date: 22.06.2010 | Approved by:
[name]
Date:22.06.2010 | Protocol No. ZYH1.09.003.01 .PROT
Version No.: 1.0 (R) |
|---------------------------------------------------------|-------------------------------------------------|-----------------------------------------------------------|

|                                                                                  |                                                                                           |              |
|----------------------------------------------------------------------------------|-------------------------------------------------------------------------------------------|--------------|
| [figure not shown] | Clinical trial Protocol for ZYH1 – Phase II
ZYH1.09.003.01.PROT

DCGI Submission | Confidential |
|----------------------------------------------------------------------------------|-------------------------------------------------------------------------------------------|--------------|

- If it is felt in Investigator's / Medical Expert's opinion that it is not in the subject's best interest to continue.
- In case a subject becomes pregnant, then she will be withdrawn from the trial.
- Subject who do not report to the clinic on +/- 4 days as per the visit schedule.
- Subject's lack of compliance to the study protocol
- Any subject who requires the use of an unacceptable concomitant medication.
- Any subject who wishes to withdraw his / her consent for participation in the study.

Subjects who, after consenting to the study, decide not to take part after administration of the first dose of study medication will retain their number. The next subject enrolled will be given the next number.

The date the subject is withdrawn from the study and the reason thereof will be documented in the CRF.

|                                                         |                                                 |                                                           |
|---------------------------------------------------------|-------------------------------------------------|-----------------------------------------------------------|
| Prepared by:
[name]
Date: 22.06.2010 | Approved by:
[name]
Date:22.06.2010 | Protocol No. ZYH1.09.003.01 .PROT
Version No.: 1.0 (R) |
|---------------------------------------------------------|-------------------------------------------------|-----------------------------------------------------------|

|                                                                                  |                                                                                           |              |
|----------------------------------------------------------------------------------|-------------------------------------------------------------------------------------------|--------------|
| [figure not shown] | Clinical trial Protocol for ZYH1 – Phase II
ZYH1.09.003.01.PROT

DCGI Submission | Confidential |
|----------------------------------------------------------------------------------|-------------------------------------------------------------------------------------------|--------------|

## 4. TREATMENTS

ZYH1 4mg will be administered in hypertriglyceridemic patients with HIV associated lipodystrophy, once daily in the morning before breakfast, for a period of 12 weeks.

### 4.1 TREATMENTS TO BE COMPARED

#### 4.1.1 Investigational product

ZYH1 4mg

#### 4.1.2 Comparator drugs(s) or intervention(s)

NA

#### 4.1.3 Dosage and treatment schedule

ZYH1 4mg will be given once orally in the morning before breakfast, for 12 weeks.

#### 4.1.4 Packaging, labelling and re-supply

The Investigational drug will be packed, labelled and supplied by CHL. The investigator will confirm the receipt of investigational drug in writing.

All drug supplies must be stored in accordance with the manufacturer's instructions separately from normal hospital / practice stocks. Drug supplies, which will not be used, are to be returned to CHL after completion of the study. All supplies must be accounted at the end of the study period.

All the centers or investigators would be provided enough number of units of the investigational drug for the conduct of the entire study. An inventory management form should be filled up for the same at the investigator's site. Investigational drug would then be dispensed to each subject in such a way that the subject can take the dosages of the investigational drug in accordance with the protocol.

|                                                         |                                                 |                                                           |
|---------------------------------------------------------|-------------------------------------------------|-----------------------------------------------------------|
| Prepared by:
[name]
Date: 22.06.2010 | Approved by:
[name]
Date:22.06.2010 | Protocol No. ZYH1.09.003.01 .PROT
Version No.: 1.0 (R) |
|---------------------------------------------------------|-------------------------------------------------|-----------------------------------------------------------|

|                                                                                  |                                                                                           |              |
|----------------------------------------------------------------------------------|-------------------------------------------------------------------------------------------|--------------|
| [figure not shown] | Clinical trial Protocol for ZYH1 – Phase II
ZYH1.09.003.01.PROT

DCGI Submission | Confidential |
|----------------------------------------------------------------------------------|-------------------------------------------------------------------------------------------|--------------|

#### 4.1.5 Storage conditions

4mg ZYH1 will be stored at room temperature.

#### 4.2 CONCOMITANT THERAPY

1. Treatment of common illness will be allowed which shall be documented in the case report form (CRF).
2. Treatment of opportunistic infections will be allowed during study period. Same will be recorded in the CRF.

##### 4.2.1 Rescue medication and additional treatment(s)

The investigator at his/her discretion will be allowed to offer a rescue medication for hypertriglyceridemia if required, however, such interventions shall be recorded in the CRF with description of type of intervention, dose and duration. If medication given is in violation to the protocol, then such subjects will be withdrawn from the trial.

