##### 4.2.2 Restrictions

1. Other lipid lowering drugs will not be allowed during the study.
2. Drugs affecting insulin resistance will not be allowed during the study.
3. Other drugs claimed for treatment of lipodystrophy will not be allowed during the study.
4. Change in antiteroviral treatment is not allowed during the study. If changes are necessary such patient will be withdrawn from study.

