## 5. OBSERVATIONS

### 5.1 EFFICACY

#### 5.1.1 Primary endpoint(s)

Percent change in TG levels from baseline to Week 6 and Week 12

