## 7. STATISTICS

### 7.1 POPULATION

#### 7.1.1 Efficacy population

##### 7.1.1.1 Intention-to-treat population (ITT):

The intention-to-treat (ITT) population will be the set of all subjects who receive study medication and have at least one post baseline efficacy data available.

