##### 7.1.1.2 Per-protocol population (PP):

The per-protocol population (PP) will be the set of all subjects who receive study medication and complete Week 12 of the study in compliance to the protocol.

The PP analysis will be considered as definitive, while the ITT analysis will be considered as supportive during the trial analysis.

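### The protocol does not settle whether a subject given rescue for hypertriglyceridemia stays or is withdrawn, and either route can overstate the TG reduction

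*Protocol*

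**What the plan says.** **Rescue and prohibited drugs.** Protocol section 4.2.1: "The investigator at his/her discretion will be allowed to offer a rescue medication for hypertriglyceridemia if required". The type, dose and duration are to be recorded in the CRF. The section closes: "If medication given is in violation to the protocol, then such subjects will be withdrawn from the trial". Section 4.2.2, the next section, states: "Other lipid lowering drugs will not be allowed during the study". The synopsis repeats that restriction and has no paragraph on rescue. Neither place exempts rescue.

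**Withdrawal.** Section 3.4 lists the grounds on which the investigator may withdraw a subject, among them: "Any subject who requires the use of an unacceptable concomitant medication". The synopsis has the same ground.

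**Endpoint and analysis sets.** The primary endpoint in section 5.1.1 is "Percent change in TG levels from baseline to Week 6 and Week 12". The PP set in section 7.1.1.2 requires subjects to "complete Week 12 of the study in compliance to the protocol", and the section adds: "The PP analysis will be considered as definitive, while the ITT analysis will be considered as supportive during the trial analysis". Section 7.2.2 and the synopsis repeat that ranking. The ITT set in section 7.1.1.1 needs subjects who received study medication and "have at least one post baseline efficacy data available". Table 1 schedules TG at screening, Week 6 and Week 12, but not at Week 2.

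**The concern.** A drug given to treat hypertriglyceridemia lowers lipids, so section 4.2.1 permits what section 4.2.2 prohibits. The closing sentence of 4.2.1 does not resolve this. It makes withdrawal depend on whether the drug violates the protocol, which is the open question. Two sites could treat identical subjects differently, and each could cite the protocol.

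Rescue is aimed at the variable that the trial measures. Each way of handling a rescued subject removes or masks a poor TG outcome, and the study has a single arm, so no control group shows how much of the TG fall is due to rescue. At stake is whether the definitive TG estimate describes ZYH1 in everyone treated, or only in those who did not need rescue, possibly with another drug's effect mixed in.

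**Working it through.** **1. The two routes, followed through the text**

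- *Rescue treated as a violation.* Section 4.2.1 requires withdrawal; section 3.4 permits it. The subject does not complete Week 12 in compliance and so leaves the PP set. This follows from the protocol's own definitions. If withdrawal comes after the Week 6 sample, the Week 6 value can still enter the supportive ITT analysis. If it comes before any post-baseline efficacy sample, the subject is in neither set.
- *Rescue treated as permitted.* The subject completes Week 12 and can remain in PP. The protocol has no rule for TG measured after rescue starts.

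Other wording adds to the uncertainty. Section 4.2.1 makes withdrawal mandatory, whereas section 3.4 makes it optional. The synopsis list of serious deviations covers prohibited drugs that subjects take on their own initiative, but does not name rescue given by the investigator.

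**2. Size, by illustration**

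The protocol gives no rescue rate and no expected TG change, so there is no figure of its own to reproduce here. Every input below is an assumption.

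- f = proportion rescued: 5%, 10%, 20%
- m = mean change in subjects not rescued: -20%
- u = mean change in rescued subjects had they not been rescued: 0% to +20%
- r = their mean change after rescue: -30%

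Formulas:

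- Mean with no rescue effect: (1 - f)m + fu
- Rescued subjects dropped: m; overstatement f(u - m)
- Post-rescue TG counted: (1 - f)m + fr; overstatement f(u - r)

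Example with f = 10% and u = +20%: 0.9 x (-20) + 0.1 x 20 = -16%. Dropping gives -20%, overstated by 0.1 x 40 = 4 points. Counting gives 0.9 x (-20) + 0.1 x (-30) = -21%, overstated by 0.1 x 50 = 5 points.

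| Rescued | No rescue effect (u = 0% to +20%) | Dropped | Counted | Overstated if dropped | Overstated if counted |
|---|---|---|---|---|---|
| 5% | -19% to -18% | -20% | -20.5% | 1 to 2 points | 1.5 to 2.5 points |
| 10% | -18% to -16% | -20% | -21% | 2 to 4 points | 3 to 5 points |
| 20% | -16% to -12% | -20% | -22% | 4 to 8 points | 6 to 10 points |

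The direction depends on u: dropping overstates the reduction when u is above m, and counting does so when u is above r. Both hold when rescue goes to poor responders.

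**3. Timing**

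TG is first scheduled on treatment at Week 6. If that value prompts the rescue, it precedes rescue, and only Week 12 is affected in a subject who is kept. Section 7.2.2 can be read as averaging Weeks 6 and 12. On that reading, in the 10% example with u = +20%, a rescued subject contributes (20 - 30)/2 = -5% instead of +20%, so the overstatement is 0.1 x 25 = 2.5 points rather than 5.

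**4. Loss of subjects under withdrawal**

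Section 3.1 gives 50 subjects for 80% power at the 5% level, without an effect size or SD, so that number cannot be reproduced. Working back for a one-sample two-sided test, 50 subjects detect a standardised change of (1.960 + 0.842)/sqrt(50) = 0.396, or 0.404 with the noncentral t distribution. At 0.404, losing 10% (45 left) brings power to 76%, and losing 20% (40 left) to 70%. This is secondary to the bias.

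**The case against.** The strongest case on the other side has four parts.

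- *The text leans towards withdrawal.* Sections 4.2.1, 4.2.2 and 3.4 can be read together: the investigator may treat, but a subject given a prohibited drug leaves the trial. That is a fair reading, and the two routes are not equally well supported. It still leaves an explicit permission beside an unqualified prohibition, and the more natural reading is the one that removes failures from the definitive set.
- *Post-rescue values are commonly handled in the SAP.* The protocol refers further analysis detail there. This stands. A reader might infer that the protocol credits post-rescue TG to ZYH1, but no section says so. The supportable statement is that the protocol does not prevent it. The SAP cannot, however, reconcile conflicting instructions to sites, and the protocol itself fixes PP as definitive.
- *Any withdrawn failure leaves PP, rescued or not.* Correct: reconciling 4.2.1 with 4.2.2 would not by itself cure the selection. That is why section 7.1.1.2 has to be part of the fix.
- *Week 6 is often untouched.* This also stands, unless an unscheduled or outside TG test prompts earlier rescue. A reader might assume that both primary time points are equally exposed; the visit schedule does not support that.

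**Conclusion.** The concern holds in this form: the protocol leaves a rescued subject's status unsettled, and that status bears directly on the primary endpoint of an uncontrolled trial. The route through withdrawal follows from the protocol's own PP definition. The route through counted post-rescue TG is possible under the protocol, falls mainly on Week 12, and may be closed by the SAP.

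Where rescue goes to poor responders, both routes overstate the TG reduction. The range of about 1 to 10 percentage points rests entirely on the assumptions in the working and is not an estimate for this trial. A reader might infer a material bias of known size. The documents do not support that, because they give neither a rescue rate nor an expected effect, and with few rescues and an unrescued change near zero the overstatement is only 1 to 1.5 points.

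**What to change.** 1. The clinical team should reconcile sections 4.2.1, 4.2.2 and 3.4 and the synopsis, so that every site handles a rescued subject in the same way. No clinical rule is proposed here.
2. Amend sections 7.1.1.2 and 7.2.2 so that rescue alone does not remove a subject from the definitive TG analysis, or make the ITT analysis definitive for TG. Changing 7.2.2 alone is not enough, because PP is defined and ranked in 7.1.1.2. The matching synopsis text must follow.
3. State in 7.2.2 that TG measured after rescue starts is not counted as ZYH1 response in the main analysis. Leave the replacement method to the trial statistician. No simple rule is clearly right: carrying baseline forward in the 10% example gives 0.9 x (-20) + 0.1 x 0 = -18% against -16%, and carrying forward the high value that prompted rescue can err the other way.
4. Add an as-observed sensitivity analysis and report the number rescued.

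The cost is protocol wording, a change to the definitive set or its definition, and a small amount of extra analysis. Rescue type, dose and duration are already recorded in the CRF. The TG estimate may be less favourable.

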##### 4.2.2 Restrictions

1. Other lipid lowering drugs will not be allowed during the study.
2. Drugs affecting insulin resistance will not be allowed during the study.
3. Other drugs claimed for treatment of lipodystrophy will not be allowed during the study.
4. Change in antiteroviral treatment is not allowed during the study. If changes are necessary such patient will be withdrawn from study.

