##### 1) Visit 1, Screening/Enrolment Visit [Week ≥ -1 to 0]

- Subjects will be screened for the inclusion and exclusion criteria and those qualifying will be invited to participate in the study.
- Clinical evaluation will be done for baseline characteristics and anthropometry.
- After Clinical evaluations all baseline safety and efficacy parameters will be recorded as per Table 1.
- All laboratory investigations will be carried out after an overnight fasting.

|                                                                  |                                                           |                                                                   |
|------------------------------------------------------------------|-----------------------------------------------------------|-------------------------------------------------------------------|
| 
Prepared by:
[name]
Date: 22.06.2010
 | 
Approved by:
[name]
Date: 22.06.2010
 | 
Protocol No. ZYH1.09.003.01 .PROT
Version No.: 1.0 (R)
 |
|------------------------------------------------------------------|-----------------------------------------------------------|-------------------------------------------------------------------|

|                                                                                   |                                                                                                   |                     |
|-----------------------------------------------------------------------------------|---------------------------------------------------------------------------------------------------|---------------------|
| [figure not shown] | 
Clinical trial Protocol for ZYH1 – Phase II
ZYH1.09.003.01.PROT
 
DCGI Submission
 | 
Confidential
 |
|-----------------------------------------------------------------------------------|---------------------------------------------------------------------------------------------------|---------------------|

- Enrolled Subjects will receive a study medication for next two weeks

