### 1.2 RATIONALE FOR CONDUCTING THE TRIAL

A variety of drugs have been studied to determine their influence on lipid profiles in patients suffering from HIV associated lipodystrophy due to HAART. Although hypolipidemic diets and physical exercise have also been found to have a role to play in the management of dyslipidemic HIV-infected patients, and are likely to be effective in this group, no randomised studies using these as monotherapy have been performed.

Recent research publications have shown the use of two lipid-lowering class of drugs, statins and fibrates, antiretroviral switching strategies and use of insulin-sensitising drugs. However, no single therapy is able to reach desirable clinical end point for HIV associated lipodystrophy. In order for firm management recommendations to be made in this setting, randomised trials are necessary.

|                                                         |                                                 |                                                           |
|---------------------------------------------------------|-------------------------------------------------|-----------------------------------------------------------|
| Prepared by:
[name]
Date: 22.06.2010 | Approved by:
[name]
Date:22.06.2010 | Protocol No. ZYH1.09.003.01 .PROT
Version No.: 1.0 (R) |
|---------------------------------------------------------|-------------------------------------------------|-----------------------------------------------------------|

|                                                                                  |                                                                                           |              |
|----------------------------------------------------------------------------------|-------------------------------------------------------------------------------------------|--------------|
| [figure not shown] | Clinical trial Protocol for ZYH1 – Phase II
ZYH1.09.003.01.PROT

DCGI Submission | Confidential |
|----------------------------------------------------------------------------------|-------------------------------------------------------------------------------------------|--------------|

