#### 1) Visit 1, Screening/Enrolment Visit [Week $\geq$ -1 to 0]

- Subjects will be screened for the inclusion and exclusion criteria and those qualifying will be invited to participate in the study.
- Clinical evaluation will be done for baseline characteristics and anthropometry.
- After Clinical evaluations all baseline safety and efficacy parameters will be recorded as per Table 1.
- All laboratory investigations will be carried out after an overnight fasting.
- Enrolled Subjects will receive a study medication for next two weeks

|                                                         |                                                 |                                                           |
|---------------------------------------------------------|-------------------------------------------------|-----------------------------------------------------------|
| Prepared by:
[name]
Date: 22.06.2010 | Approved by:
[name]
Date:22.06.2010 | Protocol No. ZYH1.09.003.01 .PROT
Version No.: 1.0 (R) |
|---------------------------------------------------------|-------------------------------------------------|-----------------------------------------------------------|

|                                                                                  |                                                                                           |              |
|----------------------------------------------------------------------------------|-------------------------------------------------------------------------------------------|--------------|
| [figure not shown] | Clinical trial Protocol for ZYH1 – Phase II
ZYH1.09.003.01.PROT

DCGI Submission | Confidential |
|----------------------------------------------------------------------------------|-------------------------------------------------------------------------------------------|--------------|

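### Other lipid-lowering drugs are banned on study, but no entry exclusion or drug-free interval protects the Visit 1 triglyceride sample, the only baseline for the primary endpoint

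*Protocol*

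**What the plan says.** The ban is in section 4.2.2 and is repeated in the synopsis under Restricted Medications: "Other lipid lowering drugs will not be allowed during the study". The same list bans drugs affecting insulin resistance and other drugs claimed to treat lipodystrophy.

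The entry criteria are in section 3.2 and are repeated in the synopsis. The TG criterion reads "Triglycerides between 200 – 500 mg"%, with no condition about lipid-lowering treatment. The only exclusion for current metabolic drugs is "Subjects on insulin and/or glitazone / glitazar therapy". The only pre-entry stability rule concerns antiretroviral therapy, which must have been stable for at least 8 weeks.

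Section 6.3 and the synopsis describe one pre-treatment visit, headed "Visit 1, Screening/Enrolment Visit [Week ≥ -1 to 0". At that visit eligibility is checked, then "After Clinical evaluations all baseline safety and efficacy parameters will be recorded as per Table 1", then "Enrolled Subjects will receive a study medication for next two weeks". Table 1 shows a single pre-treatment TG measurement; the next is at Week 6.

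The primary endpoint (section 5.1.1) is percent change in TG from baseline to Weeks 6 and 12. Section 7.1.1.2 makes the per-protocol (PP) analysis definitive and limits it to subjects who complete Week 12 in compliance. Section 3.4 lists among the reasons for withdrawal "Any subject who requires the use of an unacceptable concomitant medication".

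**The concern.** The protocol controls pre-entry drugs in two places, insulin and glitazone/glitazar use and antiretroviral stability. It does not do so for the drug class that acts most directly on the primary endpoint. As written, someone taking a statin or fibrate with TG in range can satisfy every listed entry criterion.

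If that person stops in order to comply, TG rises as the old drug wears off while ZYH1 is pulling it down. The measured change mixes the two, and a single arm has no control group to separate them. A subject who stopped shortly before Visit 1 has the same problem to a lesser degree, because the baseline is still rising. A compliant stopper stays in both the PP and the intention-to-treat (ITT) sets, so neither analysis removes the bias. If the person stays on the drug, the definitive PP set loses a subject.

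Medication history is listed as source data in section 8.2.4, so affected subjects could be identified later. Their off-drug baseline could not be recovered. That is why this belongs in the entry criteria and cannot be left to the analysis plan.

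**Working it through.** **Inputs from the protocol.** N = 50, 80% power, 5% significance (section 3.1); two-sided test (section 7.2.2); single arm (section 6.1); endpoint is percent change from baseline (section 5.1.1).

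**Inputs assumed, because the protocol gives none.** TG lowering by the stopped drug, r = 10-40%. True TG lowering by ZYH1 against untreated TG, e = 20-40%. Full rebound by the time of the follow-up sample. Share of users, f, unknown. Standard deviation (SD) of percent change, 25-50 points.

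**1. What N = 50 can detect.** The figure of 50 cannot be reproduced, since no effect size or SD is stated. Solving backwards for a one-sample comparison, (1.960 + 0.842)/√50 = 0.396 SD, or 0.404 SD with the exact t distribution. That is 10.1 points at SD 25, 16.2 at SD 40 and 20.2 at SD 50.

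**2. Shift in one affected subject.** With untreated TG = U, the on-drug baseline is (1−r)U and the follow-up value is (1−e)U.

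- Observed change = (1−e)/(1−r) − 1
- Change against an off-drug baseline = −e
- Difference = (1−e) × r/(1−r)

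| r | e = 20% | e = 40% |
|---|---|---|
| 10% | 8.9 points | 6.7 points |
| 20% | 20.0 | 15.0 |
| 30% | 34.3 | 25.7 |
| 40% | 53.3 | 40.0 |

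The range is 6.7 to 53.3 points. Where r = e, the observed change in that subject is exactly zero although ZYH1 is working.

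**3. Shift in the study mean.** Each affected subject moves the mean of 50 by 6.7/50 = 0.13 to 53.3/50 = 1.07 points. Five such subjects (illustrative, f = 10%) move it by 0.7 to 5.3 points.

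For a general f, mean = (1−f)(−e) + f[(1−e)/(1−r) − 1]. With e = 20%:

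| f | r = 10% | r = 30% | r = 40% |
|---|---|---|---|
| 0 | −20.0% | −20.0% | −20.0% |
| 10% | −19.1% | −16.6% | −14.7% |
| 30% | −17.3% | −9.7% | −4.0% |

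**4. Power.** With e = 20%, r = 30% and SD held at 40, power at N = 50 is 93% with no users, 82% at f = 10% and 39% at f = 30%.

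**5. Users who stay on the drug.** If five subjects left the PP set in this way, power for the same 0.404 SD effect would fall from 80% at n = 50 to 75.5% at n = 45. Steps 3 and 5 are alternatives for a given subject and must not be added.

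**The case against.** The best counter-argument is that the ban already works as an exclusion. Consent precedes any trial activity, and section 8.4.1 describes the course of the trial as running from signature of consent, although there it is defining adverse event collection. On that reading, someone still taking the drug when sampled is already in breach, and section 3.4 lets the investigator withdraw a subject who entered in violation. So a reader might infer that the plan intends users to be enrolled and switched as ZYH1 starts; nothing in the protocol says so. This point stands, but it does not close the gap. Under either reading no drug-free interval is required, so someone who stops at consent or shortly before still supplies an on-drug or rebounding baseline.

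The Visit 1 window is also loosely written and may allow a week or more between screening and dispensing. That does not create a later baseline, because only one pre-treatment TG is scheduled.

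The evidence that users will present is thin. Section 1.2 says "Recent research publications have shown the use of two lipid-lowering class of drugs, statins and fibrates", which describes published research and not prescribing at these sites. The share of users could be zero. The case of 30% users with 39% power shows what would have to be true for serious harm; it is not a forecast.

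The PP loss is what any five exclusions would cost. Withdrawal under section 3.4 is discretionary, and the ITT analysis remains as support. All of this limits the size of the problem without removing it.

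**Conclusion.** The gap is real and should be closed. The protocol bans a drug class that acts on the primary endpoint without protecting the only baseline sample from it. The bias runs against ZYH1.

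The size cannot be fixed from the protocol. It is about 7 to 53 points per affected subject and 0.13 to 1.1 points on the mean of 50, resting on the assumed 10-40% prior-drug effect, 20-40% ZYH1 effect and full rebound. A handful of users would shift the mean by less than the smallest change the study can detect, so the effect is modest unless users are common.

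Two stronger readings are not supported. A reader might infer a risk of a false-positive result; the direction of the bias rules that out as a consequence of this gap. A reader might also infer that a subject whose off-drug TG would exceed 500 mg% has been wrongly enrolled; the criterion as written applies to the measured value, so it is met.

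**What to change.** Add one exclusion criterion to section 3.2 and to the synopsis: use of any other lipid-lowering drug within a stated number of weeks before the Visit 1 baseline sample. Extend the same line to the other classes banned in section 4.2.2, namely drugs affecting insulin resistance beyond those already excluded and other drugs claimed for lipodystrophy. The clinical team should set the period; the 8-week stability rule already used for antiretroviral therapy is a natural model.

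No extra visit or sample is needed, because both the eligibility TG and the baseline TG then come from a subject already off these drugs. The cost is a line of text in two places and slightly slower enrolment.
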